## Abstract

**Background:**

Cardiac arrest survivors may experience hypoxic brain injury that results in cognitive impairments which frequently remain unrecognised. This may lead to limitations in daily activities and participation in society, a decreased quality of life for the patient, and a high strain for the caregiver. Publications about interventions directed at improving quality of life after survival of a cardiac arrest are scarce. Therefore, evidence about effective rehabilitation programmes for cardiac arrest survivors is urgently needed. This paper presents the design of the ALASCA (Activity and Life After Survival of a Cardiac Arrest) trial, a randomised, controlled clinical trial to evaluate the effects of a new early intervention service for survivors of a cardiac arrest and their caregivers.

**Methods/design:**

The study population comprises all people who survive two weeks after a cardiac arrest and are admitted to one of the participating hospitals in the Southern part of the Netherlands. In a two-group randomised, controlled clinical trial, half of the participants will receive an early intervention service.

The early intervention service consists of several consultations with a specialised nurse for the patient and their caregiver during the first three months after the cardiac arrest. The intervention is directed at screening for cognitive problems, provision of informational, emotional and practical support, and stimulating self-management. If necessary, referral to specialised care can take place. Persons in the control group will receive the care as usual.

The primary outcome measures are the extent of participation in society and quality of life of the patient one year after a cardiac arrest. Secondary outcome measures are the level of cognitive, emotional and cardiovascular impairment and daily functioning of the patient, as well as the strain for and quality of life of the caregiver. Participants and their caregivers will be followed for twelve months after the cardiac arrest.

A process evaluation will be performed to gain insight into factors that might have contributed to the effectiveness of the intervention and to gather information about the feasibility of the programme. Furthermore, an economic evaluation will be carried out to determine the cost-effectiveness and cost-utility of the intervention.

**Discussion:**

The results of this study will provide evidence on the effectiveness of this early intervention service, as well as the cost-effectiveness and its feasibility.

**Trial registration:**

Current Controlled Trials [ISRCTN74835019]

## Background

The incidence of cardiac arrest is 1 – 2 per 1000 inhabitants a year but differs according to country and region [1]. In the Netherlands, the incidence of cardiac arrests lies between 0.6 – 0.9 per 1000 inhabitants per year, resulting in approximately 16,000 cases of cardiac arrests each year [2,3]. Resuscitation is attempted in 30 – 50% of the cases [4]. The survival rate at discharge from the hospital after attempted resuscitations is only 9 to 16% for out-of-hospital resuscitations [2,5-7] and between 14 and 37% for in-hospital resuscitations [8-11]. Faster access to external automated defibrillators (AEDs) outside the hospital will probably raise survival rates [4,12]. This will lead to an increased number of cardiac arrest survivors and, thus, to more patients having to live with the consequences of surviving a cardiac arrest.

A cardiac arrest may lead to irreversible brain damage, called posthypoxic encephalopathy or hypoxic brain injury. Hypoxic brain injury often leads to cognitive or emotional impairments, with memory disorders and depressive symptoms being the most common complaints [13-15]. As a result of this, the performance of daily activities can be limited even six to twelve months later, with almost a quarter of the people needing some form of assistance in daily life [13,16-19]. Furthermore, participation in society often decreases after a cardiac arrest. For example, of the people who were working prior to a cardiac arrest only 20% were able to resume their job [20,21]. This all seems to result in a reduced quality of life for both the patient and their caregiver and leads to a high strain on the carer [18,20-22].

Unfortunately, although the number of problems is substantial, a large percentage of these problems, especially the cognitive impairments, are not recognised or treated.

Currently, there exist no specific follow-up programmes or nursing interventions for cardiac arrest survivors in the Netherlands. In the international literature, only a few programmes for cardiac arrest survivors were found. In a study by Cowan et al., psychosocial nursing therapy reduced two-year mortality in a group of cardiac arrest survivors [23]. This intervention consisted of physiological relaxation (biofeedback), cognitive behavioral therapy aimed at self-management and health education. Dougherthy et al. showed that an intervention, based on the principles of social cognitive theory and the concerns of patients and their partners, reduced physical symptoms and anxiety and enhanced knowledge in persons who had received an internal cardioverter defibrillator (ICD) implantation [24-26]. However, this intervention had no effect on health care use [25,26].

The diffuse brain injury and cognitive loss after a cardiac arrest seems in many ways similar to that seen after traumatic brain injury. In a study on traumatic brain injury patients, a routine follow up service resulted in a reduction in social morbidity and severity of post concussion symptoms six months later [27]. Given that cognitive impairment is a major problem in both hypoxic brain injury and moderate head injury, a comparable type of treatment could prove beneficial for patients after a cardiac arrest.

### Aims and hypotheses

The primary goal of the present study is to evaluate the effectiveness of a new, early intervention service for survivors of a cardiac arrest and their caregivers. Secondly, a process evaluation will be performed to gain insight into factors that might have contributed to the effectiveness of the intervention and to gather information about the feasibility of the programme. Finally, an economic evaluation will determine the cost-effectiveness and cost-utility of the intervention.

We anticipate that the prospective follow-up and support provided by a specialised nurse will reduce the negative consequences of a cardiac arrest and will result in a higher level of participation in society and quality of life of the cardiac arrest survivor. Furthermore, we expect that this intervention will be cost-effective.

## Methods/Design

### Study design

The study presented in this paper is a randomised, controlled clinical trial in which the effect of an early intervention service will be investigated. Participants will be followed over one year. During this year, three measurements will take place, namely two weeks, three months and twelve months after the cardiac arrest (see flow diagram, Figure 1). The Medical Ethics Committee of University Hospital Maastricht/Maastricht University approved the study protocol. The study is registered in a public trial registry [ISRCTN74835019]. This study is part of a larger research project, which also comprises a prospective and prognostic cohort study.

**Figure 1 F1:**
[figure not shown]
Study design.

### Setting

Participants will be recruited from the coronary care units and intensive care units of four hospitals in the Southern part of the Netherlands, starting in April 2007. One of the participating hospitals is a university hospital.

### Study population

The population of this study consists of cardiac arrest survivors admitted to one of the participating hospitals, including both survivors of out-of-hospital and in-hospital cardiac arrests (for in- and exclusion criteria, see Table 1) and their caregivers. In this study caregiver is defined as partner, spouse, or significant other that is most closely related to the patient.

**Table 1 T1:** Inclusion and exclusion criteria

**Inclusion criteria**
- All people who survive two weeks after a cardiac arrest
- Admitted in or to one of the participating hospitals
- Living within 50 km of one of the participating hospitals
- 18 years or older
- Sufficient knowledge of Dutch language
**Exclusion criteria**
- Life expectancy lower than 3 months (as assessed by the treating physician)
- Living in residential or institutional care prior to the cardiac arrest

The sample size calculation (two groups and one-sided testing) results from research on traumatic brain injured patients with regard to their participation in society assessed using the Community Integration Questionnaire (CIQ, described in more detail later). The mean (sd) total score on the CIQ was 16.09 (sd = 4.20) [28]. An assumed clinical relevant difference between groups of at least 10%, an alpha of 0.05 and a power (1-β) of 0.8 would necessitate 84 patients in each group. With an estimated loss to follow-up of 15%, based on earlier research in cardiac arrest survivors, 200 participants are thought to be necessary for the clinical trial [19,21,29]. This should be achievable within three years, as the area served by the participating hospitals covers approximately 1,000,000 inhabitants.

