### Statistical analysis

#### Effect evaluation

Descriptive techniques will be used to present data concerning the participants, number of dropouts, losses-to-follow up and the scores on the outcome measures.

To determine whether the patients participating in this trial are representative for the population of cardiac arrest survivors, the baseline characteristics between compliant and non-compliant participants, as well as dropouts and losses-to-follow up will be compared.

Before examining the effectiveness of the intervention, the comparability of the two groups will be checked. Baseline characteristics will be compared using independent sample T-test (normal distribution) or Mann Whitney U-test (non-normal distribution), in case of a continuous variable. In case of a dichotomous variable a chi-square test will be used.

The data from the evaluation study will be analysed according to the intention-to-treatment principle. If either T1 or T2 data are missing the 'last-observation-carried-forward' principle will be used.

Multiple regression analysis, adjusted for possible differences in baseline characteristics or baseline scores, will be applied to examine differences between the intervention and the control group on the primary outcome measures at T3 (one year after the cardiac arrest). If there is a difference between the groups, the effect size will be calculated. Subgroup analysis will be performed for potential effect modifiers.

To assess whether protocol deviations or care provided outside the intervention have caused biases, the results of the intention-to-treatment analysis will be compared to the on-treatment analysis.

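### The 80% power holds only for a one-sided 5% test that the analysis section does not carry forward; an unadjusted two-sided 5% test on the same sample has about 70%

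*Protocol article*

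**What the plan says.** The sample size paragraph under Study population (printed after the exclusion criteria) opens with "The sample size calculation (two groups and one-sided testing) results from research on traumatic brain injured patients". It takes its planning values from that source: "The mean (sd) total score on the CIQ was 16.09 (sd = 4.20"). The target is a relative difference: "An assumed clinical relevant difference between groups of at least 10" per cent. The result is that "an alpha of 0.05 and a power (1-β) of 0.8 would necessitate 84 patients in each group". Attrition is then added: "With an estimated loss to follow-up of 15%, based on earlier research in cardiac arrest survivors, 200 participants are thought to be necessary". Allocation is equal, since the abstract says that "half of the participants will receive an early intervention service".

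The primary comparison is described under Statistical analysis, Effect evaluation. Multiple regression "will be applied to examine differences between the intervention and the control group on the primary outcome measures at T3", and an effect size follows if the groups differ. That section gives no direction, sidedness, alpha or confidence level. Its adjustment is for possible differences in baseline characteristics or baseline scores. Table 3 shows that CIQ is collected for T0, the situation before the arrest, asked retrospectively at two weeks.

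Aims and hypotheses and the Discussion both state an expectation of higher participation and quality of life with the intervention.

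**The concern.** Sidedness appears once, as an input to the sample size, and is not repeated where the comparison is described. An analyst who takes the regression output in its usual form would read a two-sided p-value against 0.05. That test does not have the power the protocol states. An analyst who goes back to the sample size paragraph would use a one-sided 5% test, which admits a chance finding of benefit at 5% where a two-sided 5% test admits 2.5%.

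The two readings part on results in the favourable direction with a two-sided p between 0.05 and 0.10: a success on one, no demonstrated difference on the other. If this is not settled beforehand, the choice can be made with the result in view.

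**Working it through.** **Inputs.** From the sample size paragraph: CIQ mean 16.09, SD 4.20, difference 10%, alpha 0.05 one-sided, power 0.80, loss 15%, total 200. Allocation is 1:1 (abstract). Reading the 10% as relative to the mean is an interpretation; it is supported by the fact that it returns the stated number.

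- Difference: 0.10 × 16.09 = 1.609 points.
- Standardised: d = 1.609 / 4.20 = 0.383.

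**Step 1. Reproduce the plan's figure (one-sided 5%).**

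n per group = 2 (z₁₋α + z₁₋β)² / d² = 2 (1.645 + 0.842)² / 0.383² = 84.25. The t-test version gives 84.9.

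- Power at 84 per group: 79.9% (normal), 79.6% (t test).
- Rounded up and inflated: 2 × 85 / 0.85 = 200, the stated total.

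The plan's arithmetic stands.

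**Step 2. Same sample, two-sided 5%, unadjusted.**

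Power ≈ Φ(d √(n/2) − 1.960).

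| Per group | d √(n/2) | Normal | t test |
|---|---|---|---|
| 84 | 2.483 | 69.9% | 69.4% |
| 85 (200 × 0.85 / 2) | 2.497 | 70.5% | 70.0% |
| 100 (no loss) | 2.709 | 77.3% | 76.9% |

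For 80% power: 2 (1.960 + 0.842)² / 0.383² = 107 per group (108 by t test). With 15% loss that is 2 × 107 / 0.85 = 251.8, so 252 in total, or 2 × 108 / 0.85 = 254.1, so 255 by t test.

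**Step 3. Two-sided 5% with CIQ at T0 always in the model.**

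The residual SD becomes 4.20 √(1 − r²), so d becomes 0.383 / √(1 − r²). The protocol gives no correlation r between CIQ at T0 and at twelve months, so the values below are assumptions. Power is by t test at 85 per group.

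| r (assumed) | Adjusted d | Power |
|---|---|---|
| 0.3 | 0.402 | 74.0% |
| 0.4 | 0.418 | 77.3% |
| 0.5 | 0.442 | 81.8% |
| 0.6 | 0.479 | 87.4% |

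80% is reached at about r = 0.46 (79.9% at 0.46, 80.3% at 0.47).

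**Step 4. Where the two readings differ.**

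Standard error of the unadjusted difference at 85 per group: 4.20 × √(2/85) = 0.644 points.

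- One-sided 5% is met from 1.645 × 0.644 = 1.06 points.
- Two-sided 5% is met from 1.960 × 0.644 = 1.26 points.

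An observed benefit between about 1.06 and 1.26 CIQ points, below the planned 1.609, would therefore count as positive on one reading only.

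**The case against.** The other side has a good case. The sample size is right for the test it names, and the one-sided basis is stated openly. The Effect evaluation section does not prescribe a two-sided test: looking for differences is ordinary wording that fits either. The only statement on sidedness is the one-sided one, nothing withdraws it, and the directional expectations in Aims and hypotheses and in the Discussion fit it. A journal article may also leave the sidedness of the final test to an analysis plan. The 70% applies to an unadjusted comparison, whereas the protocol plans regression.

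Most of this stands, and it rules out three stronger readings that a reader might infer.

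- *That 84 per group is a calculation error.* It is not; Step 1 reproduces it.
- *That the two sections contradict each other outright.* They do not. One states a one-sided test and the other is silent.
- *That a one-sided test would stop the trial from reporting harm.* It would only lack a formal test for harm. The regression gives a signed estimate, and outcome scores are to be presented descriptively.

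The objection does not remove the rest. Expecting benefit is not the same as fixing a one-sided test, and neither of those sections sets a test or an alpha. The silence alone would be no finding. The point is that this document commits to a power figure depending on a lenient criterion that it does not justify, then describes the comparison without that criterion. A later analysis plan can settle the test, but it cannot give this sample 80% power in an unadjusted two-sided 5% comparison. Adjustment may recover the loss, but as worded it depends on possible baseline differences, so the gain is not assured.

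**Conclusion.** The point holds as a mismatch between sizing and analysis. The stated 80% belongs to a one-sided 5% test. For an unadjusted two-sided 5% test, power with about 170 evaluable patients is about 70%, ten percentage points lower. Fixed adjustment for CIQ at T0 would bring it to about 74% to 87%, passing 80% near r = 0.46.

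These figures rest on the protocol's own SD and difference, on 15% loss, and on a 1:1 split. The adjusted figures rest also on assumed correlations. Because T0 is a retrospective account of life before the arrest, the protocol offers no basis for picking one value in that range. The issue merits correction because it decides how a borderline CIQ result is judged; it does not show that the trial is wrongly sized for the test it names.

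**What to change.** 1. In Effect evaluation, state that CIQ at twelve months is tested two-sided at 5%, reported with a 95% confidence interval, and always adjusted for CIQ at T0 whether or not the groups differ at baseline.
2. In the sample size paragraph, keep the derivation of 84 and add the two-sided power for about 170 evaluable patients: about 70% unadjusted, and about 74% to 87% with the adjustment for assumed correlations of 0.3 to 0.6, noting that 80% needs about 0.46.
3. If one-sided 5% is kept instead, give the reason for it, state it in Effect evaluation, and report the matching 90% confidence interval.

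The cost is a less favourable stated power and a few sentences. No patients or assessments are added, because CIQ at T0 is already collected.

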### Recruitment and randomisation

Between three and ten days after the cardiac arrest the patient and caregiver will be approached to participate in the study by their treating physician. Standard procedures concerning informed consent will be used. Both patients and caregivers sign an informed consent form if they decide to participate in the study. In case the patient is still unconscious or incapacitated at the moment that informed consent is needed, the caregiver will be asked to give provisional informed consent. When the patient regains consciousness, definitive informed consent will be sought.

Participants will be randomly allocated to either the intervention group or the control group. The randomisation will take place after the baseline measurements (2 weeks after the cardiac arrest) and will be performed centrally by the project leader using a computerised block randomisation. The randomisation scheme includes prestratification on two variables, namely hospital site and location of the cardiac arrest (in-hospital versus out-of hospital). Two series of opaque numbered envelopes will be prepared for each hospital site (one for in-hospital and one for out-of-hospital cardiac arrests), filled with a card indicating the allocated group. After registration, the envelope will be opened and the specialised nurse will be informed about the patients that are allocated to the intervention group.

### Group allocation and intervention

The intervention group will receive an early intervention service delivered by a specialised nurse in addition to usual health care available to all patients, whereas the control group will only receive usual health care. The intervention period will extend up to three months after the cardiac arrest. During this period a specialised nurse will provide one to six consultations for the patient together with his or her caregiver (if present). The number of consultations will be tailored for each individual participant and will depend on the severity of the problems and the needs and wished of the patient and their caregiver. The consultations will take place in the hospital or at the participants' home. In between the consultations the participants have the opportunity to contact the nurses by phone or email. During the intervention period the specialised nurse will screen for cognitive and emotional problems. Next to that, information will be provided by means of an information booklet and by discussing questions that the participants may have. Furthermore, emotional and practical support will be offered and self-management will be explained and promoted. A consultant in rehabilitation medicine supervises the specialised nurses. If necessary, referral to additional diagnostics or specialised rehabilitation care can take place.

There will be no restrictions on possible co-interventions. Participants assigned to the intervention group who do not want treatment will still be approached for all the follow-up measurements.

### Data collection

Baseline measurements will be administered two weeks (= T1) after the cardiac arrest, with further assessments at three (= T2) and twelve months (= T3). The measurements will be administered wherever the patient is at that time. A research assistant, who will be blinded to the group allocation, will perform the assessments.

To check for the effectiveness of blinding, the research assistants will be asked after the last measurement to indicate whether they think the participant belonged to the intervention group or the control group.

### Socio-demographical and medical variables

The following socio-demographical variables will be recorded: Age, gender, nationality, marital status, living condition, educational level, and work situation. The variables related to the resuscitation and medical situation of the patient that will be recorded are presented in Table 2.

**Table 2 T2:** Variables related to the resuscitation and the medical condition of the patient.

Location of cardiac arrest
Cardiac arrest witnessed
Direct start CPR
Use of external automated defibrillator (AED)
Number of defibrillations
Time intervals
- collapse – start CPR
- call – response
- collapse – first defibrillation
- collapse – return of spontaneous circulation
Glasgow Coma Score at admission
Initial cardiac rhythm
Presumed aetiology cardiac arrest
Cardiac treatment during hospital admission e.g. mild therapeutic hypothermia, PTCA, CABG, ICD
Ejection fraction at discharge
Duration of coma
Duration post-traumatic amnesia
Cardiovascular history
Co-morbidity

### Outcome measures for the effect evaluation

The primary outcome measures of this trial are participation in society and quality of life of the cardiac arrest survivor. The secondary outcome measures are cognitive, emotional and cardiovascular impairment and daily functioning of the cardiac arrest survivor, as well as the strain, emotional functioning and quality of life of the caregiver. The instruments that will be used to measure these domains are presented in Table 3 and Table 4 and are described in the next sections.

**Table 3 T3:** Outcome domains, measurement instruments and measurement moments for the cardiac arrest survivors

			Measurement moments			
**Domain**	**Measurement instrument**	**Abbr.**	**T0**	**T1**	**T2**	**T3**

Participation in society	Community Integration Questionnaire	CIQ	X		X	X
	Impact on Participation and Autonomy	IPA				X
Quality of life	Short-Form-36 (RAND 36-item Health Survey)	SF-36		X	X	X
	EuroQol 6D	EQ-6D		X	X	X
	Quality Of Life after Brain Injury	QOLIBRI			X	X
Cognitive functioning	Cognitive Failures Questionnaire	CFQ		X	X	X
	Cognitive Log	Cog-log		X	X	X
	Adult Memory and Information Processing Battery	AMIPB		X	X	X
	Paragraph Recall	PR		X	X	X
	Trail Making Test, part A + B	TMT		X	X	X
	Verbal Fluency Test	VFT		X	X	X
Emotional functioning	Hospital Anxiety and Depression Scale	HADS		X	X	X
	Impact of Event Scale	IES		X	X	X
Cardiorespiratory functioning	New York Heart Association Classification	NYHA		X	X	X
Fatigue	Fatigue Severity Scale	FSS			X	X
Basic daily activities	Barthel Index	BI		X		
Instrumental daily activities	Frenchay Activity Index	FAI	X		X	X

T0 = situation prior to cardiac arrest (asked retrospectively at T1)

T1 = 2 weeks after cardiac arrest

T2 = 3 months after cardiac arrest

T3 = 1 year after cardiac arrest

**Table 4 T4:** Outcome domains, measurement instruments and measurement moments for the caregivers

			Measurement moments		
**Domain**	**Measurement instrument**	**Abbr.**	**T1**	**T2**	**T3**

Quality of life	Short-Form-36 (RAND 36-item Health Survey)	SF-36	X	X	X
	EuroQol 6D	EQ-6D	X	X	X
Emotional functioning	Hospital Anxiety and Depression Scale	HADS	X	X	X
	Impact of Event Scale	IES	X	X	X
Fatigue	Fatigue Severity Scale	FSS		X	X
Caregiver Strain	Caregiver Strain Index	CSI	X	X	X

T1 = 2 weeks after cardiac arrest

T2 = 3 months after cardiac arrest

T3 = 1 year after cardiac arrest

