### Primary outcome measures

#### Community Integration Questionnaire

The Community Integration Questionnaire (CIQ) is a 15-item questionnaire that assesses the level of participation in society [30]. The CIQ comprises three scales, namely home integration, productive activity, and social integration.

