#### Impact on Participation and Autonomy

The Impact on Participation and Autonomy (IPA) is a 39-item questionnaire that focuses on two aspects of participation, namely perceived participation and the experience of problems [31].

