#### EuroQol 6D

The EuroQol 6D (EQ-6D) is a generic quality of life measure consisting of 6 items (mobility, self-care, usual activities, pain/discomfort, anxiety/depression and cognition) each with three answer possibilities [32]. In addition, participants are asked to give a general rating of their current health state on a visual analogue scale, ranging from 0 to 100.

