#### Medical Outcomes Study 36-item Short Form Health Survey

The Medical Outcomes Study 36-item Short Form Health Survey (SF-36/RAND 36-item Health Survey) is a 36-item generic quality of life questionnaire that measures several domains of perceived health [33].

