## Discussion

The main goal of the ALASCA trial is to evaluate a new early intervention service for cardiac arrest survivors and their caregivers. This is a relevant topic because evidence on effective rehabilitation programmes for cardiac arrest survivors is urgently needed. During the design of this study many choices and selections were made, and four of the more important ones will be discussed.

First, the intervention was designed especially for this study. There are very few studies describing programmes for people with hypoxic brain injury due to a cardiac arrest. Consequently, we chose to model the intervention upon evidence of effective interventions for people who had traumatic brain injury, as there are many similarities between hypoxic and traumatic brain injuries [27]. This intervention designed for this study is a combination of a psychosocial intervention and a process intervention. The psychosocial aspects of the intervention are directed at providing informational, emotional and practical support and simulating self-management. The intervention is also process intervention because it is directed at providing the care needed fast and efficiently to each individual patient.

Second, the selection of our primary outcome measures, participation in society and quality of life, may differ from common primary outcome measures in cardiology research. However, this is a common approach in rehabilitation medicine, where maximisation of participation in society is one of the main goals [51]. We expect that through the care provided in the new intervention, patients will be able to reach a higher level of participation, as well as a higher quality of life.

Third, it may need some clarification why three quality of life measures will be administered. The EQ-6D and the SF-36 were chosen because they measure generic quality of life and can be used in the cost-effectiveness analyses. Next to that, these questionnaires have been used in many other patient groups, which makes it possible to compare the quality of life of cardiac arrest survivors to that of other patient groups. The third quality of life measure is the QOLIBRI, which is a brain injury specific questionnaire. This questionnaire was included because it may have a higher sensitivity to change in case of hypoxic brain injury than both general quality of life measures.

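### Five instruments are designated primary, but the 5% alpha and 80% power were derived for the CIQ total alone; the two hold together only if the CIQ alone decides, which the protocol does not say

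*Protocol article*

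**What the plan says.** The section on outcome measures for the effect evaluation sets two primary domains: "The primary outcome measures of this trial are participation in society and quality of life of the cardiac arrest survivor". Table 3 assigns two instruments to participation and three to quality of life. The section headed as primary outcome measures describes all five, and a separate heading for secondary measures follows:

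- CIQ: "The CIQ comprises three scales, namely home integration, productive activity, and social integration".
- IPA: it "focuses on two aspects of participation, namely perceived participation and the experience of problems".
- EQ-6D: "The EuroQol 6D (EQ-6D) is a generic quality of life measure consisting of 6 items", with a visual analogue rating added.
- SF-36: it "is a 36-item generic quality of life questionnaire that measures several domains of perceived health".
- QOLIBRI: a brain-injury-specific questionnaire covering six domains.

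The aims section expects that the intervention "will result in a higher level of participation in society and quality of life of the cardiac arrest survivor". The effect evaluation applies multiple regression to the primary outcomes, in the plural, at T3 (one year). It gives no order among them. The Discussion says "it may need some clarification why three quality of life measures will be administered" and explains why each was included, but does not name the one that decides.

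The sample size paragraph (Study population, after Table 1) uses one instrument: "The mean (sd) total score on the CIQ was 16.09 (sd = 4.20". With a 10% difference, one-sided testing, alpha 0.05 and power 0.8 it arrives at 84 per group, and at 200 in total after 15% loss to follow-up. The IPA and the quality-of-life instruments have no calculation.

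**The concern.** An alpha and a power describe a particular decision. Here they were worked out for one test, on the CIQ total, while five instruments carry primary status and enter the primary analysis side by side. The protocol does not settle whether success means the CIQ total alone, any one of the five, or one result in each domain. The word joining participation and quality of life in the aims can be read either way.

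The choice changes the operating characteristics. Letting any one instrument suffice raises the false-positive chance above 5%. Requiring both domains holds the 5% but takes power below 80%. While the choice is open, the decisive instrument could also be picked once the results are known.

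**Working it through.** **Inputs from the protocol.** CIQ mean 16.09 and SD 4.20; difference 10%; one-sided alpha 0.05; power 0.80; 84 per group; 15% loss; 200 in total; five primary instruments in two domains.

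**Assumptions, not in the protocol.** A common correlation r between test statistics, varied from 0 to 0.9. For power with more than one outcome, the CIQ's standardised effect is applied to the others.

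**1. Reproduce the plan's figure.**
- Difference = 0.10 × 16.09 = 1.609; d = 1.609 / 4.20 = 0.383.
- n per group = 2 × [(1.645 + 0.842) × 4.20 / 1.609]² = 84.25. The stated 84 is this value rounded down; rounding up gives 85.
- Power at 84 per group: 0.383 × √(84/2) = 2.483; 2.483 − 1.645 = 0.838; Φ(0.838) = 79.9%.
- Dropout: 168 / 0.85 = 197.6, so 198; 170 / 0.85 = 200.

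The calculation is right for the CIQ total. The issue is its scope.

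**2. Any one of k tests suffices, each at one-sided 5%.** If independent, the chance of at least one false positive is 1 − 0.95^k: 22.6% for k = 5 and 9.75% for k = 2 (one instrument per domain).

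**3. All k tests must succeed.** The false-positive chance stays at or below 5%. If independent, power at 84 per group for k = 2 is 0.799² = 64%.

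Values at r above 0, and for all five required, come from one million draws of equicorrelated normal statistics, with 84 per group for power:

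| r | Any of 5: false positive | Either of 2: false positive | Both of 2: power | All 5: power |
|---|---|---|---|---|
| 0 | 22.6% | 9.75% | 64% | 32% |
| 0.3 | 19.3% | 9.3% | 66% | 44% |
| 0.5 | 16.6% | 8.8% | 69% | 51% |
| 0.7 | 13.4% | 8.0% | 71% | 59% |
| 0.9 | 9.4% | 6.8% | 75% | 69% |

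**4. Splitting alpha instead (Bonferroni).**
- Five outcomes at one-sided 0.01: CIQ power at 84 per group is Φ(2.483 − 2.326) = 56%. Regaining 80% takes 137 per group, and 274 / 0.85 gives 323 in total.
- Two outcomes at one-sided 0.025: power 70% at 84 per group. Regaining 80% takes 107 per group, and 214 / 0.85 gives 252 in total.

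**5. CIQ total alone decides.** Alpha is 5% and power 79.9%. Of the rules examined, only this one delivers the stated pair.

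**The case against.** The strongest reply is that this is a journal article. A success rule and an alpha allocation are commonly left to the analysis plan, which is not shown and may contain them. That stands, and a reader should not infer that no rule exists. It does not dispose of the point, because what remains rests on the article's own text: five instruments are given primary status and the trial is sized on one. A later rule that shares 5% across all five by Bonferroni would leave about 56% power for the CIQ, against the stated 80%.

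Three further limits are fair.

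- A reader might infer that neither the 5% nor the 80% applies. That goes too far: an any-one rule breaks the 5% but does not lower the chance of success, a both-domains rule breaks the 80% but keeps the 5%, and a CIQ-only rule breaks neither.
- A reader might describe the error rate as several times 5%. That leans on independence, the least plausible case for overlapping measures of two domains. At correlation 0.9 it is under twice nominal, and the two-domain reading, closest to the stated primary outcomes, never exceeds 9.75%.
- A reader might count every subscale as a further primary test. The article describes the instruments' structure but does not say that subscales are tested as primary.

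Finally, the Discussion defends participation and quality of life together as a deliberate choice. Making the CIQ the gate alters that choice, so an alternative that keeps both domains is offered.

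**Conclusion.** The point holds in this form: five instruments across two domains are designated primary and are compared at T3 without order, while the one-sided 5% and 80% were derived for the CIQ total. The two figures hold together only if the CIQ total alone decides, and the article does not say so.

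The size depends on the rule. It runs from a false-positive chance of about 7% to 10% (either domain) or 9% to 23% (any of five), to power of about 64% to 75% where one instrument in each domain must succeed. Two assumptions carry these ranges: the correlations, and d = 0.383 for outcomes other than the CIQ. A smaller effect on quality of life would lower the both-domains power further. The 84 per group and the total of 200 are not in dispute for the CIQ total.

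**What to change.** By amendment, before any outcome data are seen by group:

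1. Name the CIQ total at T3 as the first confirmatory test, at one-sided 0.05.
2. Name in the same amendment one quality-of-life score, to be tested second at the same alpha and only if the CIQ test succeeds.
3. Make the IPA and the other two quality-of-life instruments secondary. All five are still collected.
4. Attach the 84-per-group and 80% statement to the CIQ total alone.

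If both domains are to stay co-primary, as the Discussion intends, name one instrument per domain, state that both must succeed, and restate the power as below 80% (about 64% to 75% under the assumptions above).

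Neither option adds patients. Under the first, a confirmatory quality-of-life claim depends on the CIQ succeeding, and quality of life remains unsized. Under the second, the trial carries a lower stated power.
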